## Abstract

**Background:**

The nephron number is thought to be associated with the outcome of chronic kidney disease (CKD). If the nephron number can be estimated in the clinical setting, it could become a strong tool to predict renal outcome. This study was designed to estimate the nephron number in CKD patients and to establish a method to predict the outcome by using the estimated nephron number.

**Methods/Design:**

The hypothesis of this study is that the estimated nephron number can predict the outcome of a CKD patient. This will be a multicenter, prospective (minimum 3 and maximum 5 years follow-up) study. The subjects will comprise CKD patients aged over 14 years who have undergone a kidney biopsy. From January 2011 to March 2013, we will recruit 600 CKD patients from 10 hospitals belonging to the National Hospital Organization of Japan. The primary parameter for assessment is the composite of total mortality, renal death, cerebro-cardiovascular events, and a 50% reduction in the eGFR. The secondary parameter is the rate of eGFR decline per year. The nephron number will be estimated by the glomerular density in biopsy specimens and the renal cortex volume. This study includes one sub-cohort study to establish the equation to calculate the renal cortex volume. Enrollment will be performed at the time of the kidney biopsy, and the data will consist of a medical interview, ultrasound for measurement of the kidney size, blood or urine test, and the pathological findings of the kidney biopsy. Patients will continue to have medical consultations and receive examinations and/or treatment as usual. The data from the patients will be collected once a year after the kidney biopsy until March 2016. All data using this study are easily obtained in routine clinical practice.

**Discussion:**

This study includes the first trials to estimate the renal cortex volume and nephron number in the general clinical setting. Furthermore, this is the first prospective study to examine whether the nephron number predicts the outcome of CKD patients. The results from this study should provide powerful new tools for nephrologists in routine clinical practice.

**Trial registration:**

UMIN-Clinical Trial Registration, UMIN000004784.

## Background

Previous studies suggested that chronic kidney disease (CKD) is one of the most important risk factors for cardiovascular disease among known other risk factors, such as diabetes, hypertension, hyperlipidemia, obesity, smoking, and lifestyle [1,2]. Furthermore, the number of the dialysis patients resulting as a consequence of the progression of CKD has been constantly increasing. Subsequently, the medical costs for treatments for end-stage kidney disease (ESKD) patients have also been increasing in Japan [3]. CKD is also regarded as a major public health problem worldwide [4].

Low birth weight (LBW) is a risk factor for the progression of kidney diseases in compliance with the Barker hypothesis [5-9]. In particular, it is well-known that glomerular changes of adults who were born with a low birth weight show focal segmental glomerulosclerosis [10]. The nephron number is correlated with the birth weight [11,12]. Therefore, the reason why the LBW affects the progression of CKD can be explained by intra-glomerular hypertension, which is induced to compensate for the small number of nephrons [13-15]. These previous data suggest that estimation of the nephron number in CKD patients can be a useful tool to predict their outcomes. However, nephrologists currently do not have any tools to determine the individual nephron number of CKD patients under normal clinical situations. Previously, estimating the total glomerular number was accomplished by a combination of magnetic resonance imaging (MRI) and a biopsy to measure the cortical glomerular volume fraction and mean glomerular volume [16,17]. However, MRI is not realistic to use in routine clinical practice because of its high cost. In addition, in spite of the fact that measuring both the cortical glomerular volume fraction and mean glomerular volume are considered to be appropriate parameters to accurately estimate the total glomerular number in individual patients, these are also unrealistic, because these procedures are very time-consuming.

This PRONEP study was designed to establish a method for predicting the renal outcome based on the nephron number estimated in patients with CKD that can be easily used in routine clinical practice. This is the first prospective study to examine whether the nephron number can predict the outcomes of CKD patients. The nephron number will be estimated by the glomerular density in biopsied samples and the volume of the renal cortex, in which glomeruli exclusively exist. In addition, this study includes one sub-cohort study to develop an equation to calculate the renal cortex volume, because there is currently no method to measure it in the typical clinical setting.

## Methods and Design

### Hypothesis

The nephron number, which is estimated from the glomerular density in kidney biopsy specimens and the volume of the renal cortex, can predict the outcome of a CKD patient (Figure 1).

**Figure 1 F1:**
[figure not shown]
**A schematic diagram of the PRONEP study**. This study is the first prospective study to determine whether the nephron number estimated by the glomerular density in kidney biopsy specimens and the volume of the renal cortex can predict the outcome of a CKD patient.

### Study design

In a multicenter, prospective (minimum 3 and maximum 5 years follow-up) study, approximately 600 patients with CKD who undergo a kidney biopsy for their diagnosis and will be enrolled from January 2011 to March 2013. These CKD patients will be recruited from 10 hospitals belonging to the National Hospital Organization of Japan. The hospitals participating in this study are spread throughout Japan (Hokkaido, Kanazawa, Chiba, Nagoya, Kyoto, Osaka, Fukuoka, and Nagasaki prefectures). This protocol was submitted to the UMIN-Clinical Trial Registration on January 1, 2011, and its unique trial number is UMIN000004784.

### Data collection at the enrollment

Enrollment should be performed at the time of the kidney biopsy after informed consent, followed by permission to participate in this study, is obtained. All patients will undergo: 1. a medical interview, 2. an ultrasound to measure the kidney size, 3. blood or urine tests, 4. a kidney biopsy to investigate the pathological findings data at the enrollment is shown in Figure 2. These examinations are performed routinely in the typical clinical setting for CKD patients receiving a kidney biopsy. In other words, no new or special examinations are included in this study.

**Figure 2 F2:**
[figure not shown]
**Registration form at enrollment**. The original Japanese form was translated to English.

In the medical interview, the question about birth weight may be difficult to answer, especially for elderly patients. If the subjects cannot answer the question about their birth weight, the question will be changed to whether their birth weight was normal (equal to or over 2500 g) or not, because LBW is defined as a newborn birth weight of less than 2500 g by the World Health Organization.

### Clinical follow-up and data collection

Patients will continue to have medical consultations and will receive examinations and/or treatment as usual. We will not direct physicians to prescribe any preferred drug, examination, or to give any specific medical advice. We will also not ban the physicians from prescribing any particular drugs.

The data for patients will be collected once a year after the kidney biopsy, and will be followed until March 2016. We will permit the data collected during the antero-posterior three months of the day of the kidney biopsy to be analyzed as well. The data collection plan is shown in Figure 3.

**Figure 3 F3:**
[figure not shown]
**Registration form to report follow-up data**. The original Japanese form was translated to English.

In this study, a cerebro-cardiovascular event was defined as an acute myocardial infarction, angina pectoris, and cerebro-vascular diseases. In addition, in order for a myocardial infarction to be reported in this study, it has to fulfill at least two of the following: (1) chest symptoms, (2) ECG changes, (3) elevated cardiac enzymes. Angina is defined as the presence of ECG abnormalities with chest symptoms and the need for catheter or surgical treatment. Furthermore, a cerebro-vascular event is defined as cases with neuropathy lasting more than 24 hours continuously and with proof of a causative lesion by CT scan or MRI (TIA and asymptomatic small infarction are not included). If no data is tracked during the follow-up, the reason will be recorded (stopped visiting the hospital, transferred to another hospital, moved to a new house, offered to stop the medical consultation, and so on).

### Parameters for the assessment

The primary parameter that will be assessed is the composite of the total mortality, renal death (starting maintenance hemodialysis and peritoneal dialysis, kidney transplantation), cerebro-cardiovascular events (ischemic heart disease, cerebral hemorrhage, cerebral infarction), and a 50% reduction in the eGFR. The secondary parameter is the rate of eGFR decline per year.

### Rationale for the number of patients

This study aims to predict the outcome of chronic kidney disease using the estimated nephron number. We assumed that the time from entry to event will be independently and exponentially distributed. The planned sample size was based on a two-tailed log-rank test with the significance level set to 0.05, and the power level set at 0.80. The ratio of low birth weight infants per total newborns in Japan was reported to be 0.086 in 1960 and 0.097 in 2007. During this period, the rate has been consistently increasing http://www.mhlw.go.jp/english/database/db-hw/vs01.html. The rate of LBW may be higher in the CKD patients than in normal subjects. We assumed that the rate of LBW would be 0.095 in the CKD patients in this study. This study is planned with an accrual interval of 2 years, and additional follow-up after the accrual interval of 3 years. The event rates were assumed to be 0.1 in the normal birth weight group and 0.2 in the low birth weight group by several studies [8,20,21]. The required sample size was therefore calculated to be 50 for the low birth weight group and 476 for the normal birth weight group [22]. Assuming that 10% of subjects would withdraw, we used the simple number of 600 as the target number of patients to recruit for this study.

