### Statistical analysis

All data are expressed as the means (SD). The primary parameter for assessment is the composite of the total mortality, renal death, cerebro-cardiovascular events, and a 50% reduction in the eGFR. We will use a Cox proportional hazard model for the analysis. We will check for confounders, interactions and multicollinearity among the independent variables. The final models will be adjusted by all significant variables, as well as confounders and other baseline covariables judged to have clinical importance. The secondary parameter is the rate of eGFR decline per year. A multivariate regression analysis will be used for the analysis. The significance level on both sides in the hypothesis testing will be set at 0.05. The analyses will be performed using the SPSS statistics software program version 19.0. (IBM Corp.)

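### The stated 80% power belongs to a low versus normal birth weight comparison that is not in the analysis plan; no power is stated for the Cox analysis of estimated nephron number

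*Protocol article*

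**What the plan says.** The Protocol article's section on the rationale for the number of patients opens by giving the aim as prediction from the estimated nephron number. Everything after that describes another exposure.

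- Test and power: "The planned sample size was based on a two-tailed log-rank test with the significance level set to 0.05, and the power level set at 0.80".
- Survival model: "We assumed that the time from entry to event will be independently and exponentially distributed".
- Effect: "The event rates were assumed to be 0.1 in the normal birth weight group and 0.2 in the low birth weight group". No time unit is given.
- Other inputs: low birth weight in 0.095 of patients, 2 years of accrual and 3 further years of follow-up.
- Result: "The required sample size was therefore calculated to be 50 for the low birth weight group and 476 for the normal birth weight group", raised to 600 for 10% withdrawal.

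The Hypothesis section reads: "The nephron number, which is estimated from the glomerular density in kidney biopsy specimens and the volume of the renal cortex, can predict the outcome". For the primary composite, the Statistical analysis section says: "We will use a Cox proportional hazard model for the analysis", with adjustment for significant variables, confounders and clinically important covariates. It names neither a log-rank test nor a comparison by birth weight.

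Birth weight is an enrollment interview item. The article concedes that "the question about birth weight may be difficult to answer, especially for elderly patients", and falls back on a yes/no question at 2500 g. The Discussion lists it as a possible input to the cortex-volume equation and, with the other enrollment data, to the outcome equations.

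**The concern.** A power statement describes one test of one contrast. Here the test (log-rank), the exposure (birth weight, split 9.5% to 90.5%) and the effect (a hazard ratio of about 2) all differ from those of the analysis that addresses the hypothesis. The Background and Discussion say that nephron number correlates with birth weight, but give no size, so the 80% cannot be carried across.

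What is at stake is how the result is read. A null finding for nephron number would naturally be set against 80% power, although no detectable effect was calculated for it. The question is also live because estimated nephron number has features that birth weight lacks:

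- Cortex volume will come from a prediction equation for most patients.
- Glomerular radius is a single value fixed from about 5% of patients.
- The model will adjust for covariates that may be correlated with the estimate.

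**Working it through.** **Inputs from the article.** Two-sided alpha 0.05, power 0.80, low-birth-weight share 0.095, rates 0.1 and 0.2, exponential times, 2 years of accrual (taken as uniform) plus 3 of follow-up, 10% withdrawal. So z = 1.960 + 0.842 = 2.802 and z² = 7.849. For hazard λ, P(event) = 1 − (e^(−3λ) − e^(−5λ))/(2λ).

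**Step 1: reproduce 50 and 476.**

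*Rates as annual probabilities.*
- λ0 = −ln 0.9 = 0.1054 and λ1 = −ln 0.8 = 0.2231, so HR = 2.12. P(event) is 0.3427 and 0.5870.
- The hazard-difference formula, with variance λ²/P(event) in each group, gives N = 7.849 × (0.08483/0.095 + 0.03239/0.905)/(0.2231 − 0.1054)² = 7.849 × (0.8929 + 0.0358)/0.01387 = 525.4.
- Split: 49.9 and 475.5, which round up to exactly 50 and 476.
- Events at 50/476: 50 × 0.5870 + 476 × 0.3427 = 192.5. Schoenfeld power = Φ(√(192.5 × 0.095 × 0.905) × ln 2.12 − 1.960) = 86%.

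*Rates as annual hazards.*
- HR = 2; P(event) is 0.3286 and 0.5477.
- Schoenfeld events = 7.849/(0.095 × 0.905 × 0.6931²) = 190. The mean event probability is 0.095 × 0.5477 + 0.905 × 0.3286 = 0.349, so N = 544. The hazard-difference formula gives 630. The fit is only approximate.
- Events at 50/476: 50 × 0.5477 + 476 × 0.3286 = 184. Schoenfeld power = 79%.

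*Rates as cumulative risks.* Over 3, 4 or 5 years, Schoenfeld power at 526 would be about 48%, 39% or 32%, so these readings do not fit.

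The rates must therefore be annual. A simulated log-rank test (5,000 runs) at 50/476 gave about 88% power under hazards and 94% under annual probabilities, so the sizing is if anything conservative for the birth-weight test. Withdrawal: 526/0.9 = 584.4, so 585, rounded up to 600. Nothing in this step involves nephron number.

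**Step 2: what the primary Cox analysis can detect.** The article gives no effect size for nephron number, so only a range is possible.

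- Evaluable patients: 600 × 0.9 = 540, i.e. 51.3 low and 488.7 normal birth weight.
- Events: 51.3 × 0.5477 + 488.7 × 0.3286 = 189 (hazards), or 51.3 × 0.5870 + 488.7 × 0.3427 = 198 (annual probabilities).
- Smallest HR per SD at 80% power = exp(2.802/√(D × (1 − R²) × reliability)), with D the number of events. R² is for nephron number on the other covariates. R² = 0.3 and reliability = 0.7 are my assumptions.

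| Case | D = 189 to 198 | D = 100 |
|---|---|---|
| Unadjusted, error-free | 1.22–1.23 | 1.32 |
| R² = 0.3 | 1.27–1.28 | 1.40 |
| R² = 0.3, reliability 0.7 | 1.33–1.34 | 1.49 |

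Examples: exp(2.802/√189) = 1.23, and exp(2.802/√(100 × 0.7 × 0.7)) = 1.49. The right-hand column represents event rates of about half those assumed, also my assumption. Halving the hazards gives 105 to 111 events in 540 patients, so 100 is a slightly pessimistic round figure.

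**The case against.** The strongest defence is that birth weight is a reasoned surrogate. The Background and Discussion argue that low birth weight means fewer nephrons and faster CKD progression. They also say that clinicians have no tool to determine an individual's nephron number, and the radius in the formula is to be fixed from study patients. A prior hazard ratio per SD of so new a measure could hardly be expected. That stands. It explains the choice of calculation, but does not make the 80% apply to nephron number, and the section does not say that a surrogate is being used.

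Two further points also stand. The Statistical analysis section does not name the Cox exposure; that it is nephron number follows from the Hypothesis, the stated aim in the sample-size section and the final step in the Discussion. And birth weight may enter an outcome equation as a covariate, although that is not the two-group comparison that was powered.

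A separate analysis plan may exist, and allowances for adjustment and measurement error could properly sit there. The point does not depend on their absence: it rests on the article presenting a complete sample-size argument tied to a different contrast.

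A reader might infer that the study is underpowered. The documents do not support this. A continuous predictor usually carries more information than a 9.5% to 90.5% split, and the detectable hazard ratios above are modest beside the assumed birth-weight ratio of about 2. A reader might also take the 79% under annual hazards as a shortfall in the article's arithmetic. It is not: annual probabilities reproduce the stated sizes exactly, with Schoenfeld power of 86%.

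**Conclusion.** The point holds as a mislabelled power claim. The 80% and the 50/476 split are sound for a log-rank test of birth weight that the analysis section does not include, and no power is stated for the adjusted Cox analysis of estimated nephron number.

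Under the article's own rates, that analysis has 80% power for a hazard ratio between about 1.22 and 1.34 per SD, depending on adjustment and measurement error. With about 100 events the range is 1.32 to 1.49. The event counts rest on annual rates and 540 evaluable patients. They make no separate allowance for biopsies with fewer than 8 glomeruli, which the article treats as insufficient for analysis. The R-squared, reliability and halved event rate are assumptions.

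Severity: should-fix. Neither the enrollment target nor the endpoint needs to change.

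**What to change.** Keep 600. In the rationale for the number of patients:

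1. Say that the 80% applies to low versus normal birth weight, used as a surrogate for nephron number, and that the size of the link between the two is not quantified.
2. Give the time unit of the rates 0.1 and 0.2, and say whether they are annual probabilities or annual hazards.
3. Add the precision of the primary analysis: about 189 to 198 expected events in 540 patients, and the smallest hazard ratio per SD of estimated nephron number detectable at 80% power, with a range over covariate R-squared, reliability and event rate, as in the table above.

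In the Statistical analysis section, name estimated nephron number as the exposure in the primary Cox model. Listing the birth-weight comparison there as a secondary analysis is optional.

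The cost is one paragraph and no new patients. The downside is small: a range replaces a single figure, so the power statement for the primary analysis becomes less definite.

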### Measurement of the kidney size by ultrasound imaging

We will record the major and the minor axis of the longitudinal plane, and the diameter of the transverse plane of the kidney by ultrasound examination as shown in Figure 4. Only the size of the biopsied site will be registered at enrollment.

**Figure 4 F4:**
[figure not shown]
**Measurement of the kidney size by ultrasound**. (**A**) We first select an image where the renal hilum is clearly observed and the area of longitudinal plane is at the maximum. In this image, the major axis (line "a") and minor axis (line "b") are measured. The line "b" should be vertical to the major axis and pass through the center of the renal hilum. (**B**) Next, we select the maximum transverse image, which is almost a circle, and passes through the center of the renal hilum. In this image, the transverse axis (line "c") is measured.

### Information from kidney biopsy specimens

As a general rule, sections stained by PAS or PAM-HE will be used for the measurement of the glomerular number and the length of the cortex (Figure 5). At the time of the measurement, squared grids will be set in an ocular lens, and thereafter, the length of the cortex will be measured. In the formal definition, the cortex and medulla are separated by the arcuate artery of the kidney. However, it is difficult to clearly discriminate between the cortex and medulla because of the frequent lack of the arcuate artery in the specimen. Therefore, we define the length of the cortex in the kidney biopsy specimen as shown in Figure 5. The needle gage number is also recorded, so that we will know the width of the specimen. The gross square area of the cortex in the specimens can be calculated by the total length of the cortex and the width. The total glomerular number and the number of glomeruli with global sclerosis will also be recorded. If the section has only one glomerulus, the section is ignored. If the total glomerular number in all sections obtained is under 8, such cases will be considered insufficient for the analysis. In line with the usual clinical procedure, the pathological diagnosis will be performed and registered.

**Figure 5 F5:**
[figure not shown]
**Definition of the length of the cortex in this study**. (**A**) The length of cortex is measured from the outermost glomerulus to the innermost glomerulus. (**B**) When the medulla is sandwiched between cortices, the total of two lengths between the outermost glomerulus to the innermost glomerulus is considered the length of the cortex in the section.

### Estimation of the total nephron number in a kidney

Based on previous studies, we will first assume that there is 31% volume shrinkage in the paraffin-embedded specimens due to fixation in formalin [17,23,24]. Therefore, we will take the quotient of the actual measured values of the length by $0.883\;\left(=\sqrt[{3}]{1-0.31}\right)$ for the calculation below. Next, the volume of the glomerulus is thought to shrink 43% in the biopsied specimens because of the loss of arterial pressure and because of paraffin embedding after fixation in formalin [16,17,23,24]. Therefore, the actual axis of the glomerulus is calculated by dividing the measurement axis by $0.829\left(=\sqrt[{3}]{1-0.43}\right)$, and the value is used for the numerical formula below.

The total number of glomeruli is estimated as follows:

The formula of the spherical volume can be derived using integral calculus, i.e. disk integration to sum the volumes $\text{V}\;\text{ = }\;\int_{-r}^{r}\pi \left(r^{2}-x^{2}\right)dx=\frac{4}{3}\pi r^{3}$, where r is radius of the sphere, and π is the constant pi.

Similarly, the average area of the observed glomeruli on one section in the biopsied specimen is estimated as follows:

We assume that glomeruli less than 5 micrometers in diameter cannot be counted. A sphere 2r in diameter is cut off at both ends in parallel so that the diameter of a section may be set to 2r_o_(5 μm). We observe only circles parallel to the section of this solid, whose height is defined as 2 h. Considering a 2 h-high cylinder whose volume is equal to this solid, the cylindrical base area is equal to the average cross-sectional area of this solid cut at random parallel to the base of the solid (Figure 6).

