**Figure 6 F6:**
[figure not shown]
**A hypothetical sphere of a glomerulus**.

$${\text{A}}_{\text{h}}\times 2\text{h = }\int_{-\text{h}}^{\text{h}}\pi \left({\text{r}}^{2}\text{ - }\;{\text{x}}^{2}\right)\text{dx}$$

where A_h _is the average rea of the observed circle. Hence, A_h _is estimated by:

$${\text{A}}_{\text{h}}=\frac{1}{2\text{h}}\int_{-\text{h}}^{\text{h}}\pi \left({\text{r}}^{2}\text{ - }{\text{x}}^{2}\right)\text{dx = }\frac{\pi }{2\text{h}}{\left[{\text{r}}^{2}\text{x - }\frac{{\text{x}}^{\text{3}}}{3}\right]}_{-\text{h}}^{\text{h}}=\frac{\pi }{2\text{h}}\left(2r^{2}\text{h - }\frac{2}{3}{\text{h}}^{3}\right)=\pi \left({\text{r}}^{2}-\frac{{\text{h}}^{2}}{3}\right)$$

Using the Pythagorean theorem, $\text{h}=\sqrt{{\text{r}}^{2}-{\text{r}}_{\text{o}}{}^{2}}$

Where r is the glomerular radius and r_o _is the cut-off value of the observed glomerular radius (Figure 6).

Substituting h with a function of r and r_o _gives:

$${\text{A}}_{\text{h}}=\pi \left({\text{r}}^{2}-\frac{\left({\text{r}}^{\text{2}}-{\text{r}}_{\text{o}}^{2}\right)}{3}\right)=\pi \left(\frac{2}{3}{\text{r}}^{2}+\frac{1}{3}{\text{r}}_{\text{o}}^{2}\right)$$

A_cortex_s _(Area of the cortex of the section in a biopsied specimen) is calculated as:

$${\text{A}}_{\text{cortex\_s}}={\text{L}}_{\text{a + b}}\times {\text{d}}_{\text{b}}$$

Where d_b _is the internal diameter of the biopsy needle and L_a+b _is "a + b" in Figure 5 for the total cortex length in biopsied specimens.

VF _glom/cortex _(Volume fraction of glomeruli/cortex) is equal to AF_glom/cortex _(Area fraction of glomeruli/cortex on the section).

$$\text{V}{\text{F}}_{\text{glom}/\text{cortex}}=\text{A}{\text{F}}_{\text{glom}/\text{cortex}}=\frac{{\text{N}}_{\text{s}}\times {\text{A}}_{\text{h}}}{{\text{A}}_{\text{cortex - b}}}$$

Where N_s _is the number of observed glomeruli in a biopsied specimen.

Finally, the total number of glomeruli (N_total_) was calculated as:

$${\text{N}}_{\text{total}}\;=\;\frac{\text{Total}\;\text{glomerular}\;\text{volume}}{\text{one}\;\text{average}\;\text{glomerular}\;\text{volume}\;}\;=\;\frac{\text{V}{\text{F}}_{\text{glom/cortex}}\;\times \;{\text{V}}_{\text{Cortex}}}{\frac{4}{3}\;\pi {\text{r}}^{3}}$$

Where V_cortex _is the volume of the cortex estimated by MRI.

In this study, the value of r will be decided after calculating the means of approximately 5% of the attending patients by random sampling. Therefore, "r" is not a variable in the final calculation.

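### In the nephron-number formula the glomerular radius is rescaled by 0.829 but the count is left at its shrunken height; this step alone lowers every absolute N_total by about 6%

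*Protocol article*

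**What the plan says.** The calculation is written out in the Protocol article, *Estimation of the total nephron number in a kidney*, and in the formulas that follow Figure 6.

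- Tissue: "we will first assume that there is 31% volume shrinkage in the paraffin-embedded specimens due to fixation in formalin". For lengths, "Therefore, we will take the quotient of the actual measured values of the length by" 0.883, the cube root of 1 − 0.31.
- Glomerulus: "the volume of the glomerulus is thought to shrink 43% in the biopsied specimens because of the loss of arterial pressure" and because of embedding. "Therefore, the actual axis of the glomerulus is calculated by dividing the measurement axis by" 0.829, the cube root of 1 − 0.43, and the result goes into the formulas as r.
- Section area: A_cortex = L × d_b, where d_b "is the internal diameter of the biopsy needle and L_a+b" is the total cortex length.
- Count: N_s "is the number of observed glomeruli in a biopsied specimen". No correction to it is given.
- Total: N_total = (N_s × A_h / A_cortex) × V_cortex / ((4/3)πr³), with A_h = π((2/3)r² + (1/3)r_o²). V_cortex "is the volume of the cortex estimated by MRI", so it is on the in vivo scale.
- The radius is one study-wide value, from the mean in about 5% of patients: "Therefore, 'r' is not a variable in the final calculation".

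**The concern.** A glomerulus may well shrink more than the tissue around it, so having two shrinkage factors is not in itself a fault. The difficulty is where the second factor is used. The formula multiplies a count made with shrunken glomeruli by the cross-section of a full-size glomerulus, then divides by a full-size volume. If glomeruli really had their in vivo size, a section would hit more of them, and N_s would be larger. N_s is not raised to match, so the two scales do not cancel.

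Estimating the nephron number in CKD patients is a stated aim of the study (Abstract, *Background*). A fixed scale error would carry into every absolute number reported, into any regression coefficient per fixed number of nephrons, and into any cut-off or comparison set beside counts made by another method, such as the published range per kidney quoted in the *Discussion*.

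**Working it through.** **Inputs.** All come from the section named above: tissue volume shrinkage 31%, glomerular volume shrinkage 43%, linear factors k = 0.883 and g = 0.829, and a smallest countable profile of 5 µm diameter (r_o = 2.5 µm). Assumption: d_b is the fresh core width and is not divided by 0.883, which is how A_cortex = L × d_b reads most naturally. Subscript s marks the embedded section. D is the true number of glomeruli per unit volume of fresh cortex.

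**1. The stated factors.** (1 − 0.31)^(1/3) = 0.8837, printed as 0.883. (1 − 0.43)^(1/3) = 0.8291, printed as 0.829. Both reproduce, apart from a truncation of 0.07% in the first.

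**2. What r does in the formula.** The r_o term is negligible: at an assumed r of 100 µm it is 2.5²/(2 × 100²) = 0.03% of the main term. Then

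N_total = N_s × (2/3)πr² × V_cortex / (A_cortex × (4/3)πr³) = N_s × V_cortex / (2r × A_cortex).

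So 2r is only the height over which a plane can cut a glomerulus.

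**3. What the count measures.** On the embedded section, N_s = D_s × 2r_s × A_s. Shrinkage raises the density to D_s = D/k³, and the restored area is A_cortex = A_s/k². Hence

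N_s/A_cortex = D × 2r_s/k, so D = (N_s/A_cortex) / (2r_s/k).

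The radius needed here is r_s/0.883.

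**4. What the protocol uses.** With r = r_s/0.829, the ratio of the protocol's result to the true value is g/k = 0.829/0.883 = 0.939, or 6.1% too low. The correction factor is 0.883/0.829 = 1.065.

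**5. Check through the volume fraction.** On the stated shrinkages the in vivo glomerular fraction is 0.69/0.57 = 1.211 times the section fraction. The protocol's route gives (0.883/0.829)² = 1.135 times. The quotient 1.135/1.211 is again about 0.94. An area correction has been applied where a volume correction was needed.

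**6. Numerical checks.** With the full formula, including r_o and unrounded cube roots, the ratio is 0.938 at every assumed in vivo radius tried from 60 to 150 µm. With r_s divided by the tissue factor it is 0.9997 to 1.0000. A simulation of sectioned, shrunken spheres gave 0.941 with the protocol's radius and 1.002 with r_s/0.883.

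**7. Dependence on d_b.** Estimated/true N_total, from this step and the width together:

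| Treatment of d_b | As written | With r_s/0.883 |
|---|---|---|
| Fresh width, undivided | 0.939 | 1.000 |
| Fresh width, but divided by 0.883 | 0.939 × 0.883 = 0.829 | 0.883 |
| Really the embedded width, undivided | 0.939/0.883 = 1.063 | 1/0.883 = 1.133 |

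**8. Effect on the models.** If each N is 0.939 times its true value, a Cox log hazard ratio per fixed number of nephrons is 1/0.939 = 1.065 times what it would otherwise be. The hazard ratio per SD or per unit of log N does not change.

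**The case against.** The strongest case on the other side is that this changes nothing the study sets out to test. The radius is one constant, so the error is one multiplier common to all patients. The hypothesis is that nephron number predicts outcome, and the analyses are a Cox model and a multivariate regression. Ranking, p-values, discrimination and fitted risks are unaffected. An equation or threshold derived with this formula and later applied with the same formula gives the same predictions, because the coefficient absorbs the constant. The document plans no preset absolute cut-off and no formal comparison with other counts. The range of 227,327 to 1,825,380 in the *Discussion* is background on an eight-fold spread, against which 6% is small. All of this stands.

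The second objection is that 6% is not the whole error. It depends on how d_b is read (step 7), and on one reading the sign of the combined error reverses. Other simplifications act too. Cortex length is measured from the outermost to the innermost glomerulus, which leaves out glomerulus-free cortex at the ends and pushes N up. There is no section-thickness term: if sections are 2–4 µm thick and glomeruli 150–200 µm across (assumed values), N_s is about 1–3% too high. This also stands. It limits the claim to one factor but does not remove that factor, which is present on every reading of d_b.

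That the article is condensed is no answer here, because both constants and the whole formula are printed.

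**Conclusion.** The step is wrong as written. It combines an in vivo glomerular size with a count made at the shrunken glomerular height. On the protocol's own 31% and 43%, with L divided by 0.883 and d_b taken as the fresh width left undivided, this factor alone makes every absolute N_total about 6% too low (0.939).

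Three stronger readings are not supported:

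- A reader might infer that reported nephron numbers will be 6% below the truth overall. The other simplifications and the unstated treatment of d_b leave the net error unestablished.
- A reader might infer that the test of the hypothesis or the prediction equation is compromised. With r constant, neither is. Only absolute numbers, coefficients per fixed number of nephrons, and cut-offs or comparisons carried to counts made by other methods are affected.
- A reader might infer that the shrinkage factors are miscalculated, or that there should be only one. Both cube roots reproduce and both may be right; the fault lies in where 0.829 is used.

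This is a minor correction, worth making because the nephron number is the study's central measurement.

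**What to change.** In *Estimation of the total nephron number in a kidney*:

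1. Divide the measured glomerular axis by 0.883 where r enters the N_total formula. Multiplying N_s by 0.883/0.829 = 1.065 and leaving r as it is gives the same N_total.
2. Keep 0.829 only for reporting an in vivo glomerular volume in its own right.
3. With r_s/0.883, do not report VF_glom/cortex as an in vivo fraction. It then equals the section fraction, and the in vivo value is 1.211 times that.
4. State that d_b is taken as the fresh core width and is not divided by 0.883. This belongs with item 1: if d_b were really the embedded width, changing r alone would move the result from 1.063 to 1.133 times the true value.

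The cost is one constant and two or three sentences. No new data are needed. Every N_total rises by 6.5%, and values already calculated can be rescaled.
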